## Abstract

**Methods/design::**

This multicenter, randomized control trial will enroll 200 patients at 4 hospitals in Japan undergoing ESD for colorectal epithelial tumors. Patients who meet the inclusion and exclusion criteria will be randomized to undergo ESD using S-O clips or conventional ESD. Patients will be randomized by a computer-generated random sequence with stratification by operator experience (trainee or expert), tumor location (colon/rectum), and institution. The primary endpoint will be ESD procedure time, defined as the time from the start of the local injection into the submucosal layer to the end of dissection. Other outcomes will include the rates of procedural complications, en bloc resection and cure.

**Discussion::**

ESD using the S-O clip is expected to shorten procedure time, reduce the incidence of adverse events, and standardize the procedure. This study may resolve clinical questions about whether ESD using the S-O clip traction device is more effective and safer than conventional ESD.

## 1. Introduction

Endoscopic submucosal dissection (ESD) is a technique that allows the en bloc resection of colorectal epithelial tumors regardless of size. Although ESD is minimally invasive and provides favorable outcomes, it is technically difficult to perform, due in part to a lack of maneuverability, and requires a long procedure time. In addition, patients undergoing colorectal ESD are at particularly high risk of complications due to the thin bowel wall, bowel flexion, and peristalsis, with prolonged colorectal ESD increasing the risk of complications such as perforation.^[1–3]^ Moreover, the colon is more susceptible than the esophagus and stomach to fibrosis caused by peristalsis and biopsy, especially in patients with recurrent lesions after EMR, with high fibrosis making the procedure more difficult. Patients may also experience postoperative fever and abdominal pain, even in the absence of obvious perforation, due to the transfer of heat during the procedure from the radiofrequency device to the muscle layer and serosa, a condition called post-ESD electrocoagulation syndrome (PECS). The incidence of PECS in patients undergoing gastric ESD has been reported to be 7.1%, but to be much higher, ranging from 12.1% to 40%, in patients undergoing colorectal ESD.^[4–7]^ Risk factors for PECS include long procedure time, lesion location other than in the rectum or sigmoid colon, tumor diameter >3 cm, and segmental resection.^[2,8,9]^ Therefore, the risk of PECS may be reduced by shortening the procedure time and minimizing the effect of thermocoagulation on the muscle layer.

Direct visualization of the submucosal layer, such as by traction of the lesion during mucosal dissection, may make ESD easier to perform. Several techniques involving traction of the lesion have been reported to be effective in ESD for early-stage colorectal cancer.^[10,11]^ One of these traction devices, the S-O clip (Zeon Medical, Tokyo, Japan), pulls the lesion in the intended direction in the lumen. The S-O clip can be passed through the working channel, allowing the lesion to be pulled independently of the endoscope. The S-O clip tractions the lesion toward the lumen and facilitates direct visualization of the submucosal layer, with the traction effect and adequate dissection depth allowing efficient dissection^[12]^ (Fig. 1). This traction device may shorten procedure times and reduce the risks of complications such as PECS. A single-center, randomized, controlled study performed at the institution that developed the S-O clip reported that use of the S-O clip in colorectal ESD significantly shortened the procedure time.^[8]^ To our knowledge, however, no multicenter randomized controlled trials have assessed the usefulness of the S-O clip in colorectal ESD. This clinical study was therefore designed to evaluate the usefulness of the S-O clip in colorectal ESD and assess the effects of this clip on procedure time and rate of complications.

**Figure 1. F1:**
[figure not shown]
Photograph and schema of the S-O clip traction device. The spring effect provides continuous traction on the lesion, facilitating visualization of the avulsed surface.

## 2. Methods/design

### 2.1. Study aims and design

This prospective randomized clinical trial involving 4 medical institutions in Japan was designed to compare the efficacy and safety of the ESD procedure using the S-O clip with conventional ESD in patients with colorectal epithelial neoplasia.

### 2.2. Patients

At each institution, the on-site study investigators will enroll candidates who provide written informed consent, enter the required information into the electronic data collection system, verify that each candidate meets the eligibility criteria (i.e., the meets all inclusion criteria and none of the exclusion criteria), and register the candidate with the registration office. After confirming that the candidate meets the eligibility criteria, a registration number will be assigned. Once enrollment is complete, patients will be randomized 1:1 to undergo ESD using the S-O clip or conventional ESD. Patients will be stratified by 3 factors: ESD surgeon (trainee/expert), institution, and lesion site (rectum/colon).

### 2.3. Inclusion criteria

Patients will be included if they are aged ≥ 20 years, have an Eastern Cooperative Oncology Group Performance Status of 0 to 3, and have a colorectal epithelial tumor determined by colonoscopy to be an indication for ESD. Tumor size, morphology, circumferentially, and fibrosis are not required inclusion criteria. Lesions indicated for colorectal ESD will consist of those that require en bloc endoscopic resection and meet the 2014 colorectal ESD/EMR guidelines.^[14]^ These lesions will include the laterally spreading tumors-nongranular (LST-NG), lesions with a type VI pit pattern, T1 (SM) mildly invasive carcinomas difficult to resect en bloc by snare EMR, large depressed tumors, large raised lesions with suspected cancer, intramucosal tumors with fibrosis in the submucosa, sporadic localized tumors resulting from chronic inflammation, as in ulcerative colitis, and local residual early stage cancer after endoscopic resection. All patients must be fully informed and understand the requirements for study participation and provide voluntary written informed consent.

### 2.4. Exclusion criteria

Patients will be excluded if pre-operative examinations show indications of deep submucosal invasion; if the lesion is preoperatively diagnosed as a neuroendocrine tumor; if the tumor cannot be visualized in its entirety even with inversion; if the tumor crosses the anal canal, terminal ileum, appendix, or diverticulum; or if patients are eligible for ESD of ≥ 2 with colorectal tumors. Patients will also be excluded if their platelet counts are < 50,000/μL; if they are taking 2 or more antiplatelet agents or an anticoagulant other than warfarin; or if they are taking warfarin with a PT-INR ≥ 2.6, or a PT-INR ≥ 3.0 following mitral valve replacement surgery.^[13,14]^ Patients will also be excluded if they have serious complications in other organs, defined as an American Society of Anesthesiologists physical status ≥ 4; are pregnant; or are deemed ineligible for any other reason by the principal investigator or sub-investigator.

### 2.5. Randomization and blinding

Patients will be randomly assigned 1:1 to undergo ESD using the S-O clip or traditional study treatment groups using a minimization method. Randomization will be performed by dynamic balancing using the minimization method, with stratification by operator experience (trainee or expert), tumor location (colon/rectum), and institution. Neither patients nor physicians will be blinded to patient allocation. Endoscopists who have performed < 40 ESD procedures will be considered trainees, whereas those who have performed > 40 ESD procedures will be considered experts. Trainees who have performed < 40 colorectal ESD procedures are required to perform at least 5 of these procedures prior to the start of the study, with gastric ESD experience not required. In addition, each experts and trainee is required to perform at least 1 colorectal ESD with the S-O clip prior to the start of the study.

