### 2.6. ESD procedures

The endoscope will be inserted into the colon; after identifying the lesion, its periphery will be marked when necessary. Solution will be injected into the submucosa and submucosal dissection will be continued until completion. There were no restrictions regarding endoscopes, needles, hemostats, and hoods, although only the Dual Knife (Olympus) was allowed for marginal incisions and submucosal dissection. Upper endoscopy was allowed, depending on the situation. EMR on other polyps was allowed before or after ESD on the same day. To ensure patient safety, for patients in whom it is impossible to complete the procedure, the trainee could be replaced by a specialist, thus allowing the procedure to continue. Trainees assigned to a procedure that has lasted more than 60 minutes but who are unable to continue the assigned procedure will be allowed to switch to the other procedure. Physicians having difficulty completing conventional ESD within 60 minutes will be allowed use of the S-O clip midway through the procedure. Conversely, physicians having difficulty completing ESD with the S-O clip within 60 minutes, due to interference by the S-O clip, will be allowed to remove the clip. Antithrombotic medications will be withdrawn or replaced according to gastrointestinal endoscopic practice guidelines.^[7,15]^

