### 2.7. Primary endpoint:

The primary endpoint of this study will be procedure time, defined as the interval from the start of local injection into the submucosal layer until the completion of dissection.

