### 2.8. Secondary endpoints:

Several secondary endpoints will be evaluated. The first is the incidence of procedural complications (i.e., intraoperative perforation, delayed perforation, post-bleeding, PECS), defined as the ratio of the number of procedure-related complications to the total number of patients in the efficacy analysis population. PECS in the absence of obvious perforation will be defined as localized tenderness plus fever > 37.6°C, white blood cell count > 10.000/mm^3^, or C-reactive protein concentration ≥ 0.5 mg/dL within 6 hours after ESD. Posterior hemorrhage will be defined as a ≥ 2 g/dL decrease in Hb concentration or overt bleeding requiring endoscopic hemostasis, but not as a small amount of blood in the stool. Perforation will be defined as a total tissue defect that allows free passage to the body cavity, regardless of the presence of free air on radiographic examination.

Other secondary endpoints will include the *en bloc* resection rate, defined as the percentage of lesions resected en bloc without segmental resection; and the cure resection rate, defined as the percentage of resected specimens that meet all the following criteria on pathological evaluation: negative horizontal and vertical margins (complete resection); histological type such as papillary adenocarcinoma, ductal adenocarcinoma, or adenoma; evaluation of intramucosal carcinoma or submucosal invasion showing that the distance of submucosal invasion is < 1000 μm; and negative for lymphovascular and vascular invasion. Another secondary endpoint in patients who undergo ESD with the S-O clip will be the time from the start of traction with the S-O clip to the completion of detachment. An additional secondary endpoint will be the conversion rate, defined as the percentage of patients undergoing conventional ESD who required S-O clip placement during the procedure and the percentage of patients undergoing ESD with the S-O clip who required S-O clip removal. Finally, the incidence of adverse events will be evaluated.

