#### 3.2.2. Evaluating secondary endpoints.

The complication rate will be defined as the rate of complications associated with the procedure. The frequencies and percentages of complications associated with the procedure, as well as the batch resection, cure, conversion, and adverse event rates will be tabulated for each group. Summary statistics (mean, standard deviation, minimum, median, maximum) from the time of S-O clip traction to the completion of dissection will be calculated for the S-O clip group.

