## 4. Discussion

ESD is a well-established technique that enables en bloc resection regardless of the size and morphology of the lesion.^[16–18]^ Although improvements in endoscopists’ skills and endoscopic equipment have increased the use of ESD for lesion removal, endoscopic manipulation remains difficult, with slight manipulations associated with a risk of complications. Perforation during colorectal ESD can cause peritonitis and require emergency surgery, emphasizing the importance of improving safety. Risks of perforations are higher when lesions are located vertically rather than tangentially, because, in the former, the tip of the knife approaches the submucosa perpendicularly. Safe and rapid dissection requires maintenance of an appropriate submucosal view that is as parallel to the muscle layer as possible. Thus, lesions require pulling in an effective direction. Conventional ESD uses a gravitational traction method that relies on changes in posture. Because this conventional method often cannot maintain sufficient traction, it often fails to maintain an appropriate submucosal view. This increases the difficulty of procedure increases, leading to an increased risk of complications. ESD using the S-O clip uses an endoscope and an independent device to maintain sufficient traction of the lesion in a short time regardless of lesion location. It has the advantage of allowing free manipulation of the scope.

This multicenter randomized controlled trial will evaluate the usefulness of the S-O clip in colorectal ESD by comparing the procedure time and frequency of complications with those obtained during conventional colorectal ESD. If use of the S-O clip shortens the procedure time and reduces the frequency of procedural complications, it may contribute not only to reducing the physical burden on patients, but also to shortening hospital stays and lowering costs. Although the number of facilities that can perform colorectal ESD is currently limited, safer performance of this procedure will allow it to become more widely performed. The major limitation of this trial will be that the operator will not blinded to treatment group allocation.

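### Patients are expressly left unblinded and no masked assessor is named, although PECS on its natural reading needs localized tenderness in every case

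*Protocol article*

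**What the plan says.** Section 2.5 (Randomization and blinding) states the rule outright: "Neither patients nor physicians will be blinded to patient allocation". It makes no exception for whoever examines the patient after the procedure.

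Section 2.8 lists procedural complications first among the secondary endpoints, and PECS is one of the four. It opens the definition with "PECS in the absence of obvious perforation will be defined as localized tenderness plus fever > 37.6°C" and then adds a white cell count and a C-reactive protein threshold, joined by an or. Section 2.8 also defines cure as "the percentage of resected specimens that meet all the following criteria on pathological evaluation", without saying who reads the specimens or what they know about the arm.

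Section 3.2.2 plans frequencies and percentages of procedure-related complications, "as well as the batch resection, cure, conversion, and adverse event rates will be tabulated for each group". It states no test.

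Section 4 (Discussion) describes the blinding as follows: "The major limitation of this trial will be that the operator will not blinded to treatment group allocation". It does not mention the patient. Sections 4 and 5 nevertheless look to the trial for an answer on complications and safety as well as on procedure time.

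**The concern.** The operator cannot be blinded to a traction device that he or she places. The documents give no comparable reason why the patient should know the arm, yet section 2.5 makes patient unblinding a rule.

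This matters for PECS because tenderness is elicited. The patient reports or reacts, and an examiner decides whether that counts. The Introduction and the Abstract put in print the hope that the clip lowers PECS and adverse events. If that expectation makes patients or examiners slower to report or record tenderness after a clip procedure, the clip arm will show fewer PECS cases with no true effect. The fever and laboratory criteria guard against over-calling. They cannot restore a case in which tenderness was never recorded, and no later analysis can remove the difference.

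A reader who relies on the Discussion alone would think that only the operator knew the arm, and would give a PECS difference more weight than the design supports.

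**Working it through.** **Setting the text side by side.**

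1. Who is unblinded. Section 2.5 names patients and physicians. Section 2.6 uses the second word for the endoscopists who operate: "Physicians having difficulty completing conventional ESD within 60 minutes will be allowed use of the S-O clip midway through the procedure". Section 4 names the operator. So physicians may mean operators only, but patients are unblinded on any reading.
2. What PECS needs. The natural reading of section 2.8 is tenderness plus any one of fever, raised white cell count or raised C-reactive protein. Tenderness is then necessary for every case. Another parsing, with tenderness tied to fever only, is grammatically possible but less natural.
3. Who examines for tenderness. The article does not say. Section 2.6.1 requires operators to be principal investigators or sub-investigators, and nothing stated separates them from those who assess outcomes.

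**Illustration of size.** The plan gives no figure on this point, and its sample size calculation concerns procedure time, which blinding does not enter. The inputs are:

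- PECS rate p: the Introduction gives a range, "ranging from 12.1% to 40%, in patients undergoing colorectal ESD". Both ends are used.
- Patients per arm n: 200 in total (section 3.1), allocated 1:1 (section 2.2), so 100.
- Relative under-recording r in the clip arm: **assumed** to be 10%, 20% or 30%. The documents give no value and no direction.
- True effect on PECS: assumed to be none.

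Spurious difference: d = p × r.

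Standard error of a difference with equal rates: SE = √(2p(1−p)/n).

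- p = 12.1%: √(2 × 0.121 × 0.879 / 100) = 0.046, or 4.6 points.
- p = 40%: √(2 × 0.40 × 0.60 / 100) = 0.069, or 6.9 points.

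For scale only, the last column gives the chance that a nominal two-sided 5% test, **which the plan does not state**, would favour the clip. With q = p(1−r) and p̄ the mean of p and q, this is Φ[(d − 1.96·SE₀)/SE₁], where SE₀ = √(2p̄(1−p̄)/n) and SE₁ = √((p(1−p) + q(1−q))/n). Example for p = 40%, r = 20%: q = 32%, p̄ = 36%, SE₀ = 0.0679, SE₁ = 0.0676, giving 0.216. Without bias the chance would be about 2.5%.

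| p | r | d (points) | d / SE | chance of favouring the clip |
|---|---|---|---|---|
| 12.1% | 10% | 1.2 | 0.26 | 4.5% |
| 12.1% | 20% | 2.4 | 0.52 | 7.9% |
| 12.1% | 30% | 3.6 | 0.79 | 13.2% |
| 40% | 10% | 4.0 | 0.58 | 8.4% |
| 40% | 20% | 8.0 | 1.15 | 21.6% |
| 40% | 30% | 12.0 | 1.73 | 43.2% |

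At the low end of the PECS range the bias stays below one standard error throughout. It exceeds one standard error only at the high end, and only with under-recording of 20% or more.

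**The case against.** Four objections carry weight.

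- **The endpoint is secondary and descriptive.** The plan says "The primary endpoint of this study will be procedure time", and complications are only tabulated. No stated inference is corrupted. This stands, and it limits the importance of the point. It does not remove it, because sections 4 and 5 intend conclusions on safety and a tabulated difference will be read that way.
- **The open design is disclosed.** Calling operator unblinding the major limitation does not deny others, so a reader who infers a flat contradiction between sections 2.5 and 4 goes too far. What stands is that the limitation leaves out the patient, whom section 2.5 expressly includes.
- **The bias is hypothetical.** The amount of under-recording, its direction and its restriction to one arm are assumptions. The Introduction says only that the device may reduce PECS, and no text shows that patients share this view. This stands in full: the table shows what could happen, not what will.
- **Masking the examiner may not be free.** Since the article does not say who examines for tenderness, the operators may do it themselves, and a masked examiner would then be extra staff. This stands, and it is why the fix below makes that step conditional. Withholding the arm from the patient does not depend on it.

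Two stronger readings are tempting. A reader might infer that every physician, including ward staff, is told the arm. Section 2.5 does not say so, and section 2.6 uses the word for operators. A reader might also infer that pathologists read the cure criteria knowing the arm. The article does not state what they know, and a condensed article commonly leaves this to the full protocol, so no bias in the cure rate can be claimed.

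**Conclusion.** The point holds in a limited form. Section 2.5 expressly unblinds the patient and names no masked assessor, for a complication that on the natural reading cannot be diagnosed without tenderness, and the limitation stated in the Discussion is narrower than the rule in section 2.5.

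Its possible size, under the assumed 10% to 30% under-recording with no true effect, runs from 1.2 to 3.6 points at a PECS rate of 12.1% and from 4 to 12 points at 40%, that is, from about 0.3 to 1.7 standard errors. The result rests on reading the PECS criteria as tenderness plus any one of three signs, and on under-recording that occurs in the clip arm alone. Neither procedure time nor the sample size is touched. This is an inexpensive improvement to the credibility of a safety comparison, not a flaw in the primary analysis.

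**What to change.** - Reword section 2.5 so that the operator and procedure-room staff know the arm and the patient is not told it until the last evaluation, with immediate disclosure if care requires it.
- Where existing staff other than the operator examine for tenderness, have them record it on a page that does not show the arm.
- Send the pathology request without the arm, and state whether pathologists are masked.
- Reconcile the limitation in the Discussion with section 2.5, so that it names everyone who knows the allocation.

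The cost is the wording of section 2.5 and the Discussion, the consent text, and the layout of the tenderness record and pathology request. Withholding the arm from the patient needs no extra staff, procedure or patients. The downside is that masking may be imperfect, for example if a clip is seen on imaging; the report should then describe PECS as only partly protected.

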### 2.6. ESD procedures

The endoscope will be inserted into the colon; after identifying the lesion, its periphery will be marked when necessary. Solution will be injected into the submucosa and submucosal dissection will be continued until completion. There were no restrictions regarding endoscopes, needles, hemostats, and hoods, although only the Dual Knife (Olympus) was allowed for marginal incisions and submucosal dissection. Upper endoscopy was allowed, depending on the situation. EMR on other polyps was allowed before or after ESD on the same day. To ensure patient safety, for patients in whom it is impossible to complete the procedure, the trainee could be replaced by a specialist, thus allowing the procedure to continue. Trainees assigned to a procedure that has lasted more than 60 minutes but who are unable to continue the assigned procedure will be allowed to switch to the other procedure. Physicians having difficulty completing conventional ESD within 60 minutes will be allowed use of the S-O clip midway through the procedure. Conversely, physicians having difficulty completing ESD with the S-O clip within 60 minutes, due to interference by the S-O clip, will be allowed to remove the clip. Antithrombotic medications will be withdrawn or replaced according to gastrointestinal endoscopic practice guidelines.^[7,15]^

